### Power Calculation

We conducted an *a priori* power analyses to determine the number of clusters (schools) for the trial as well as the number of participants (students and teachers) per cluster. Following a previous trial of ICC-T at Tanzanian secondary schools (21), we expected moderate (δ = 0.25) and large effects (δ = 0.35) on student-reported and teacher-reported violence by teachers, respectively. Based on previous and ongoing trials of ICC-T (3, 20, 21), we expected an intra-class correlation coefficient (ICC) of 0.03 and 0.05 for student- and teacher-reported violence, respectively. Moreover, the covariance between baseline and follow-up scores of violence at the school level was *r* = 0.30. Given all specified parameters (α = 0.05; power = 0.80; effect size students: δ = 0.25, effect size teachers: δ = 0.35; ICC students = 0.03, ICC teacher = 0.03; *R* = 0.30), no drop out at the school-level and an estimated dropout rate of 30% for teachers and 25% for students, in total 36 schools with 28 students and 13 teachers per school are required to detect the expected effects. The total sample size is therefore at least *n* = 1,008 children and *n* = 468 teachers.

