### Schools

Selected schools must meet the following inclusion criteria: (1) teachers should not have received any training on violence prevention in the past; (2) the school should be a community or public mixed-gender school; (3) the school should have at least 13 teachers and at least 40 children in the 4th class of primary school (see power calculation above). In case of fewer than 13 teachers or fewer than 40 students in the relevant grade, the selected school will be combined with a neighboring school (within 15 km) into a school cluster. Schools that meet these criteria will be listed in alphabetical order and a random selection of six schools/school clusters in each of the six communes of Haiti's Département du Nord will be executed using http://www.random.org. In each commune, three schools or school clusters will be allocated to the treatment group (i.e., teachers will receive the ICC-T sessions), and the other three schools or school clusters into the control group (i.e., teachers will not receive the ICC-T sessions) after baseline assessment. All random selections and allocations will be performed by independent research staff.

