### Assessment Procedures

As part of the recruitment process, the implementing partner—P4H Global, a Haitian NGO providing training programs to teachers in Haiti—will visit the selected 36 schools to advertise the study, meeting first with the school principals. These visits serve to check the inclusion criteria for schools and to ensure the willingness of principals to participate in the study.

The local partner will shortly return to schools to register and enroll the teachers and the children. To ensure common and clear understanding of the relevant details of the study, the local partner will provide information to selected students and voluntarily participating teachers in a formal information session. Parental informed consent will be sought for each selected student through information sessions for parents at the school or through letters sent out to parents. After baseline, schools will be allocated into treatment and control groups, and the program will be delivered to those in the treatment group after the baseline (pre-) assessment is completed.

Data will be collected from both control and treatment schools. Both teachers and children will be surveyed. Data collection will take place in three stages: (i) t_0_, at baseline – before the intervention; t_1_, 6 months after the intervention; and t_2_, 18 months after the intervention. Each data collection phase will take approximately two and a half months. Data will be collected using tablet-based surveys and the software Survey-to-go (22). Since floor effects were detected in the feasibility study, surveys will not be self-administered but conducted as interviews in Haitian Creole. A team of enumerators (external to the local partner facilitators so that results are not contaminated) will be trained in the use of this survey methodology and the collection of data. The local partner leadership will recruit and supervise the enumerators, who will be trained prior to the implementation of the program by the research team. Enumerators should be native Haitians, fluent in both English and Haitian Creole and ideally have a background in psychology, pedagogy, education, or related disciplines. The local partner and the research team will provide onsite supervision structure to this team of enumerators through the duration of the study. Enumerators will be blind regarding the allocation of the schools.

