### Statistical Analysis

Pre-assessment data will be used to assess the prevalence of maltreatment and violence as well as children's mental health and well-being. A longitudinal analysis (including the follow-up assessments) will then be undertaken using an intent-to-treat approach. As drop-outs and missing data at follow-up assessment are likely given the longitudinal study design, we aim to apply full information maximum likelihood estimation to obtain unbiased parameter estimates.

Our main analysis of the primary and secondary outcomes will be time × group interaction effects using multilevel linear modeling. By randomly assigning schools to the intervention and control condition, we do not expect systematic differences between schools, teachers, and students in the two groups. However, we will examine differences between the groups in sociodemographic characteristics on the level of the school (e.g., material conditions), teachers (e.g., socioeconomic status, teaching experience) and students (e.g., socioeconomic status, gender). In case of significant differences, we will control for these differences in all analyses. Latent growth modeling or cross-lagged path models will be used to estimate the directional influence of violence by teachers on primary and secondary outcome variables over time. Results will be presented including appropriate effects sizes and with a measure of precision (95% confidence intervals). Effect sizes of η^2^ ≥ 0.01, η^2^ ≥ 0.06 and η^2^ ≥ 0.14 will be considered as small, moderate, and large effects, respectively (47).

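### Sociodemographic covariates for all analyses are chosen by significance tests of chance baseline differences, so the covariate set depends on the data and not on prognosis

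*Protocol article*

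**What the plan says.** All of the following is in the protocol article.

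- **Model (Statistical Analysis).** "Our main analysis of the primary and secondary outcomes will be time × group interaction effects using multilevel linear modeling". The same section sets intention to treat and full information maximum likelihood.
- **Premise (Statistical Analysis).** Because schools are randomised, "we do not expect systematic differences between schools, teachers, and students in the two groups".
- **Rule (Statistical Analysis).** Despite this, "we will examine differences between the groups in sociodemographic characteristics on the level of the school (e.g., material conditions"). Teacher examples (socioeconomic status, teaching experience) and student examples (socioeconomic status, gender) follow. Then: "In case of significant differences, we will control for these differences in all analyses".
- **Timing (Assessment Procedures).** "After baseline, schools will be allocated into treatment and control groups".
- **Stratification (Schools).** "In each commune, three schools or school clusters will be allocated to the treatment group", and the other three go to control, in each of six communes.

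Five characteristics are named, all as examples, so the list is open. The section gives no test, no significance level and no allowance for multiple comparisons. It names no covariate that enters whatever the test shows.

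**The concern.** A significance test of a baseline difference asks whether the arms differ by more than chance. When allocation is random and follows the measurement, that answer is known beforehand: chance is the only cause. The section says as much in its premise and then makes adjustment depend on the test.

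Covariates are worth adjusting for when they predict the outcome, and the p-value of the baseline comparison carries no information on that. The rule therefore brings in a characteristic unrelated to violence if it happens to be imbalanced. It leaves out a strongly prognostic one that happens to be balanced enough.

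What is at stake is pre-specification and the useful choice of covariates. The covariate set behind every primary and secondary estimate cannot be written down until the baseline tests are run. Because list, test and level are all open, two analysts following the text could arrive at different sets.

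This is a rule that the article states and ties to all analyses, so it is not a detail left to an unseen analysis plan.

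**Working it through.** **1. Inputs.** From the article: 36 schools, 28 students and 13 teachers per school, dropout 25% and 30%, "α = 0.05; power = 0.80", "effect size students: δ = 0.25, effect size teachers: δ = 0.35", and 0.30 for the baseline to follow-up relation at school level (Power Calculation); five example characteristics (Statistical Analysis). Assumed: 0.05 per baseline test, independent tests, ICC 0.05 for the tested characteristics. The article's ICCs, 0.03 and 0.05, refer to violence.

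**2. The plan's own figure.** The article gives no figure for the covariate rule, but its sample size shows how much spare power there is. SE = √{4[ICC(1 − R²) + (1 − ICC)/m]/36}, with ICC 0.03 as entered in the calculation, 0.30 read as R², and m after dropout (28 × 0.75 = 21; 13 × 0.70 = 9.1).
- Students: √[4(0.0210 + 0.0462)/36] = 0.0864; 0.25/0.0864 = 2.89; power 0.803 (t, 34 df).
- Teachers: √[4(0.0210 + 0.1066)/36] = 0.1191; 0.35/0.1191 = 2.94; power 0.815.

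The 36 schools are reproduced, with almost nothing to spare.

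**3. How often the rule fires by chance.** P(at least one) = 1 − 0.95^k. For the five examples, 1 − 0.95⁵ = 0.226. Five candidates allow 2⁵ = 32 covariate sets. Any one characteristic, however prognostic, is adjusted for in about 5% of trials.

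**4. If the tests ignored schools.** The design effect is 1 + (m − 1)ICC, and the true rejection rate is 2[1 − Φ(1.96/√DE)].
- Teachers: DE = 1 + 12 × 0.05 = 1.60; 1.96/1.265 = 1.549; rate 12.1% (simulation 12.6% to 12.8%).
- Children: DE = 1 + 27 × 0.05 = 2.35; 1.96/1.533 = 1.279; rate 20.1% (simulation 19.9% to 20.1%).

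School-level items such as material conditions have no such inflation.

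**5. Effect on the treatment test.** A simulation used 36 school means at a single follow-up, one school-level covariate and 8,000 runs per setting. It is a simpler setting than the plan's time × group model.

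| Covariate–outcome correlation | Type I error, test then adjust | Type I error, always adjust | Power, test then adjust | Power, always adjust |
|---|---|---|---|---|
| 0.3 | 0.046 | 0.046 | 0.79 | 0.82 |
| 0.5 | 0.042 | 0.047 | 0.80 | 0.89 |
| 0.7 | 0.037 | 0.051 | 0.80 | 0.97 |

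Type I error is at or below nominal under the rule. In this setting the gain from a prognostic covariate is almost entirely lost.

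**6. Effect on the time × group term.** Generalised least squares with known variances, 36 schools, 28 children, one follow-up, a fixed characteristic entered as a main effect, correlation about 0.5, 300 runs.
- Complete data: estimate and SE are the same with and without the covariate.
- Random 25% dropout: mean shift in the estimate 0.008 (largest 0.032); SE 0.0964 without and 0.0959 with the covariate.

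**The case against.** The strongest defence is that the rule does little harm in this model. The core analysis is pre-specified and only add-on covariates vary. The target is a change over time, and a fixed characteristic entered as a main effect drops out of within-person change, as step 6 shows. This stands. The power gains in step 5 must not be carried over to the plan's model: they would need covariates that bear on the time × group term, and the section does not say how covariates enter.

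Three stronger readings are tempting, and the documents do not support them.

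- **Inflated type I error.** A reader might infer this from any data-driven model choice. The simulation gives 0.037 to 0.046.
- **Loss of baseline violence or commune as predictors.** The rule covers sociodemographic characteristics only. Baseline violence already enters as the t0 response, and commune is balanced by design, three schools against three. Of the obvious candidates, only child gender falls under the test.
- **Baseline tests sure to fire far more often than 5%.** That holds only if they ignore schools. The section names no test for this comparison, and the one method it names for the main analysis is multilevel.

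The defence does not reach the logic of the rule, which selects on a quantity unrelated to prognosis and contradicts the section's own premise.

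**Conclusion.** The point holds as a fault of pre-specification and covariate choice with a modest numerical effect. The adjustment set depends on chance imbalance and cannot be written down in advance.

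The rule would add at least one of the five example characteristics by chance in about 23% of trials, assuming independent tests at 0.05. A longer list raises this: 40% for ten. The rates of about 13% for teachers and 20% for children rest on two further assumptions, tests that ignore schools and an ICC of 0.05.

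The effect on the main estimate is small as long as covariates enter only as main effects. It could be larger if they were crossed with time, which the section leaves open. The change is worth making because it costs almost nothing.

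**What to change.** 1. Delete the sentence that makes adjustment depend on significant differences.
2. Fix one covariate set before follow-up data are seen: commune (the allocation stratum) and, for child outcomes, gender (already a sampling stratum). Cross each with time, so that it bears on the time × group effect.
3. Use the baseline outcome once. Either keep t0 as a response and constrain the arms to a common t0 mean, which random allocation after baseline justifies, or use it as a covariate with only t1 and t2 as responses. Adding it as a covariate while t0 is also a response would count it twice.
4. Present baseline characteristics by arm descriptively, without tests.
5. Keep any adjustment for observed imbalance as a labelled sensitivity analysis.

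Item 3 may bring the larger gain. With equal variances and 0.30 read as a correlation, an unconstrained change contrast has relative variance 2(1 − 0.30) = 1.40, against 1 − 0.30² = 0.91 with baseline adjustment. With 0.30 read as R² (r = √0.30 = 0.548) the figures are 2(1 − 0.548) = 0.90 and 1 − 0.30 = 0.70.

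Cost: no new data and no change in sample size. Commune takes five degrees of freedom at school level (34 to 29), and the model specification changes slightly.

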### Intervention Description

In the treatment condition, ICC-T will be delivered as a 5-day training workshop (9 h per day). Drawing on attachment, behavioral and social learning theories, ICC-T provides teachers with practical information and tools to prevent the use of violent disciplinary strategies in class and to improve their interaction competencies with children. Workshop sessions are divided into five modules (12): (1) improving teacher-student interactions, (2) maltreatment prevention, (3) effective discipline strategies, (4) identifying and supporting burdened students, and (5) implementation of ICC-T components in everyday school life. Sessions about *teacher-student interactions* aim to increase teachers' understanding of children's behavior, raise awareness of their responsibility of being a role model for students and foster positive teacher-student communication and interaction. Sessions on *maltreatment prevention* aim to raise awareness of the negative consequences of violent discipline for children's well-being. Teachers are encouraged to reflect on their own experiences of violent discipline as a child and to connect their own experiences and feelings to their current discipling behavior and its consequences. Sessions on *effective discipline strategies* aim to equip teachers with practical tools on how to maintain and reinforce desired behaviors of students and how to change misbehavior. The sessions on *identifying and supporting burdened students* aim to raise teachers' awareness of common internalizing and externalizing problems of children and to provide strategies how to support children with these problems in the school context. Finally, in the sessions on *implementation* teachers are encouraged to devise ways of how they can apply the ICC-T components in everyday school life and to create long-term support strategies to promote the sustainability of the intervention content.

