### Study Measures

Following established international guidelines, Haitian Creole native speakers will translate all the forms and measures from English into Creole and then back into English in a blind written form. The back-translated items will then be compared with the original items to verify that the translation has been correctly undertaken and the content is equivalent. To ensure high objectivity and reliability during data assessment, standardized procedures on questionnaire administration will be developed and implemented. All surveys will be undertaken in Haitian Creole. Prior to data collection, a pilot study in one primary school (which will not be included in the trial) will be conducted to ensure the feasibility of the questionnaire administration.

The main outcome measure is teachers' use of violence. This will be measured in two ways: (i) teachers' self-reported use of violence, and (ii) children's self-reported experiences of violence. Secondary outcome measures are teachers' attitudes toward violent discipline, children's mental health problems and quality of life as well as their cognitive performance. Additionally, we will assess children's experiences of peer violence, social competence and their academic performance through a standardized literacy and numeracy test and children‘s scores in Mathematics, Creole-French, Science, Social science, and General Studies in the mid-term. These scores will be provided by the school administration.

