Haiti is an example that legal bans and international conventions may be necessary, but not sufficient to stop violence against children in the school setting (48). We argue that it is crucial to address attitudes and norms about the violent discipline of children as well and to work together directly with educators. A reduction of violence in the school setting has also shown to precede a wider societal change in attitudes and behaviors regarding corporal punishment in various countries (49). The study will be conducted against the backdrop of political turmoil in Haiti following the assassination of the president in July 2021 and amid a precarious humanitarian situation that has been aggravated by the earthquake in August and by the ongoing Covid-19 pandemic. As research indicates an increase of multiple risk factors for violence against children in the wake of political conflict, disasters and the pandemic (50), programs aiming to prevent violence against children in their most important social settings, i.e., at school and at home, are sorely needed.

Our primary outcome of interest is teachers' use of violence against children in the past week. As teachers' reports of violence may be biased in the same direction as the intervention effect, we also consider students' self-reports of violence by teachers. We expect the reduction of teachers' use of violence to be reflected in a change of the secondary outcome of teachers' attitudes toward violent discipline. The choice of secondary outcomes on the students' side is based on the assumption that a school environment characterized by less violence by teachers will have positive effects on students' mental health, quality of life and cognitive abilities. Moreover, we expect that a lower use of violence by teachers will also lead to less victimization by peers, as teachers are likely to act as non-violent role models for children. We assume that the long-follow up interval of 18 months will be enough time for these effects to unfold. As the use and experience of violence are sensitive topics, we expect socially desirable responses to be a relevant issue in spite of societal norms in favor of violent discipline. Therefore, adequate training of enumerators in recognizing and dealing with social desirability is crucial. We opted for structured interviews as assessment method as this will allow enumerators to get more valid and accurate answers on the topics of interest.

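### An ordinary cross-lagged path, or a pair of correlated growth slopes, cannot by itself show directional influence of teacher violence; report these paths as associations or use a within-child model

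*Protocol article*

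**What the plan says.** The Statistical Analysis section of the protocol article describes two layers of analysis. The first is the main one: "Our main analysis of the primary and secondary outcomes will be time × group interaction effects using multilevel linear modeling". The second concerns the link between violence and the other variables: "Latent growth modeling or cross-lagged path models will be used to estimate the directional influence of violence by teachers on primary and secondary outcome variables". The section does not choose between the two model families. It does not say whether stable differences between children are separated from change within a child, or whether allocated arm enters the model.

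Four other places bear on the point.
- Study Measures makes violence the primary outcome: "The main outcome measure is teachers' use of violence".
- Assessment Procedures sets three waves at unequal spacing: "before the intervention; t_1_, 6 months after the intervention; and t_2_, 18 months after the intervention".
- Intervention Description says that the sessions on burdened students are meant "to provide strategies how to support children with these problems in the school context", the problems being internalizing and externalizing ones.
- The Discussion gives the premise behind its choice of child secondary outcomes: "a school environment characterized by less violence by teachers will have positive effects on students' mental health, quality of life and cognitive abilities". The models in the second layer are the only stated analysis of that link.

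**The concern.** The question asked is whether exposure to teacher violence alters a child's later outcome. An ordinary cross-lagged model tests something else: whether earlier violence predicts the later outcome once one earlier, imperfectly measured outcome score is held fixed. A single lagged score does not remove a stable difference between children, so part of that difference can remain in the cross path.

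The protocol makes such differences plausible. Violence, mental health problems (PSC-Y) and quality of life (KIDSCREEN-10) are all reported by the same child in an interview, and the Discussion expects socially desirable answering. Home adversity or a harsher school could act in the same way.

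A growth model fails differently. It has a level and a slope for each child, but an association between two slopes does not say which variable moves first.

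Two further faults sit in the same sentence. Teacher violence is the primary outcome, so its influence on the primary outcome is circular or undefined. The sessions on burdened students may also change child outcomes without passing through violence; if arm were left out of the model, that route would be credited to violence. At stake is a mechanism claim resting on a path that can be significant when no lagged effect exists.

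**Working it through.** **The plan's own figures.** The article gives no figure for the directional models, only the trial size: 36 × 28 = 1,008 children. For students it uses "α = 0.05; power = 0.80; effect size students: δ = 0.25, effect size teachers: δ = 0.35", an ICC of 0.03 and R = 0.30. After 25% dropout there are 21 children per school. Reading R as the share of school-level variance explained, the variance of the difference is 2[(1 − 0.03)/21 + 0.03 × (1 − 0.30)]/18 = 0.00747, so SE = 0.0864 and 0.25/0.0864 = 2.89. On 34 df, two-sided 5%, power is 0.80, so the stated size reproduces. The number used below is 36 × 21 = 1,008 × 0.75 = 756.

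**Assumed inputs.** The only stability figure in the article is 0.30 at school level. The child-level values are therefore assumptions: stable share of variance τ (the same for both variables), correlation of the stable parts ρ, autoregression of the changing part a, and same-wave correlation of the changing parts w. Both variables have variance 1 and are scored so that higher is worse. The true cross-lag is zero.

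**Formula.** Write:
- c = τρ + (1 − τ)w, the same-wave correlation;
- r = τ + a(1 − τ), the outcome's correlation with its previous wave;
- d = τρ + a(1 − τ)w, the correlation of the outcome with earlier violence.

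The cross-lagged coefficient is b = (d − rc)/(1 − c²) = τ(1 − τ)(1 − a)(ρ − w)/(1 − c²). It is zero only if there are no stable differences (τ = 0), the variables are wholly stable (τ = 1 or a = 1), or ρ = w. It is positive when ρ exceeds w and negative when w exceeds ρ.

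**One case in full** (τ = 0.5, ρ = 0.5, a = 0.2, w = 0.1):
- c = 0.30, r = 0.60, d = 0.26;
- b = 0.25 × 0.8 × 0.4/0.91 = 0.088;
- residual variance 1 − (0.36 + 0.0676 − 0.0936)/0.91 = 0.633;
- SE = √(0.633/(756 × 0.91)) = 0.0303, so z = 2.90;
- rejection rate Φ(2.90 − 1.96) = 83%.

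**False-positive rate per path, n = 756, a = 0.2, w = 0.1**

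| Stable share τ | ρ = 0.2 | ρ = 0.3 | ρ = 0.5 |
|---|---|---|---|
| 0 | 5% | 5% | 5% |
| 0.3 | 8% | 18% | 56% |
| 0.5 | 11% | 29% | 83% |
| 0.7 | 11% | 31% | 87% |

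**Sensitivity at τ = 0.5**
- a = w = 0: 36%, 68% and 99% at ρ = 0.2, 0.3 and 0.5.
- ρ = 0.5, a = 0.2, w = 0.3: 32%. With w = ρ the rate is 5%.
- ρ = 0, a = 0.2, w = 0.3: b = −0.061, rejected 55% of the time, in the opposite direction.
- Rough allowance for clustering: design effect 1 + 20 × 0.03 = 1.6, effective n = 472. With a = 0.2 and w = 0.1 the rates are 9%, 20% and 63%.
- Either of the two lags significant (simulated, a = 0.2, w = 0.1): 48% at ρ = 0.3 and 98% at ρ = 0.5.

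A simulation with 36 schools, school variance 0.03 and cluster-robust tests (ρ = 0.5, w = 0.1, a = 0.1) gave 55% and 56% for the two paths at stable share 0.3, and 80% and 82% at 0.5. Clustering lowers the rates but does not remove the problem.

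**With a random intercept per child.** Likelihood-ratio tests rejected 7.3% (ρ = 0.3) and 8.0% (ρ = 0.5) of 400 runs at τ = 0.5, with Monte Carlo error about 1.3 points. A separate fit in two settings rejected 3% of 200 runs in each. These rates lie near 5%, on either side of it.

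**Growth models** (approximated by child-level slopes at 0, 6 and 18 months, stable correlation 0.5). With w = 0, slope-on-slope was significant in 4.9% of runs and level-on-slope in 4.5%, so stable differences alone cause no inflation. With w = 0.1, slope-on-slope was significant in about 78%. That is a genuine same-time association, but it has no direction.

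**The case against.** The strongest reply is that this is a condensed article. A random-intercept model is itself a cross-lagged path model, so the wording does not exclude it; random intercepts, clustering, arm terms and lag constraints are commonly left to an analysis plan. That stands as far as the detail goes. Nothing in the article says that arm would be omitted. What remains is that the sentence promises directional influence from two model families that, in their ordinary form, do not deliver it.

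A reader might infer that a false directional finding will usually result. The documents do not support that. They give no child-level stability or correlations, and the rate returns to 5% when the same-wave correlation of the changing parts equals the stable correlation (with equal stable shares). Above that point the false path turns negative and would not favour the mechanism in the Discussion. Answering in the same interview could raise that same-wave correlation too.

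A reader might also place growth models under the same fault. The calculation shows otherwise.

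The shared-reporter argument is weaker for cognition and academic performance, which are measured by tablet tasks, a standardised test and school marks. Finally, the random-intercept model was tested on data generated from its own structure, with normal scores and no school effect, so its good showing is partly by construction.

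**Conclusion.** The point holds in a limited form. The stated aim, directional influence, is not delivered by an ordinary cross-lagged model when stable differences between children are correlated, nor by correlated growth slopes. For the cross-lagged option the false-positive rate per path with 756 children can lie anywhere from 5% to over 90%. It exceeds 50% at a stable correlation of about 0.5 with weak same-wave correlation, or at a lower stable correlation if the changing parts are nearly independent. These figures rest on assumed child-level values, equal stable shares, normal scores and, in the closed form, no school effect. They show what can happen, not what will.

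The circular reference to primary outcomes and the possible route from arm to child outcomes outside violence follow from the text without any assumed figure. A reader might infer that the trial's effectiveness result is in doubt. It is not: the time × group comparison between randomised schools does not use these models. The weakness is confined to the mechanism claim, and it should be corrected before data are analysed.

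**What to change.** Change the sentence in Statistical Analysis in four ways.

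1. Either report the paths from a plain cross-lagged or growth model as exploratory associations, or, if a within-child lagged effect is wanted, specify a cross-lagged model with a random intercept per child for each variable, standard errors clustered on school, and lag paths free to differ between the 6-month and 12-month intervals.
2. Include allocated arm as a predictor at the two follow-ups in either model.
3. Delete the words *primary and*, so that the targets are the secondary outcomes only.
4. State that conclusions about the effect of ICC-T come only from the randomised comparison.

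The cost is wording; the three planned waves suffice and no new data are needed. The associational option gives up only the directional claim. The random-intercept option brings wider confidence intervals and possible convergence problems, since there are only three waves and the article itself describes the violence items as extremely skewed. It should not be made mandatory.
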